### Method of Data Collection Procedures

The principal investigator (PI) and co-investigators (telenurses) received training in telenursing such as communication and behavior modification techniques, and self-management skills on diabetes including blood sugar control and foot care. They will receive study-specific training from other coinvestigators and one diabetic consultant on data collection such as how to collect data and what type of tool has to be used during data collection. The patients who will attend the PHCs and telenurses will identify the patients with diabetes by checking the patient’s blood test report. They will check the participants’ eligibility criteria (inclusion and exclusion criteria) and obtain written informed consent. It will be ensured that there will be no risk in disclosing the information.

They will educate patients using an investigator-developed “Education Booklet” at the PHCs. The booklet will be given to the patients after receiving consent and health education will be provided at the time as scheduled (Multimedia Appendices 1 and 2). The data will be collected within a 6-month study period using:

“Initial assessment sheet” developed by the investigators. It will be filled out once by the telenurses in the PHCs to assess the patient’s initial condition and to set the goals for their behavior change. This contains sociodemographic, clinical history, and lifestyle.“Self-monitoring book” developed by the investigators (Multimedia Appendix 3). Patients will complete their daily life activities including their laboratory investigation reports at home. The telenurses will educate and guide them on how to fill it over telecommunication. This contains daily practice goals (eg, energy intake, salt, exercise, ideal weight), laboratory data record (eg HbA_1c_, fasting blood sugar [FBS] or random blood sugar [RBS], lipid profile, and renal function), foot care (monthly check), daily recording (RBS if needed, blood pressure, medication intake, daily goal achievement of diet and exercise) and behavior change goals (monthly).“Diabetes management self-efficacy scale” developed by Bijl et al [20] and has 20 items with a 5-point Likert scale from 1-5. The scores range from 20 to 100, a higher point indicates better self-efficacy.The “Lifestyle behavior questionnaire” developed by the investigators has 6 items with a 6-point Likert scale from 0 to 5, a higher point indicates a better lifestyle. This is asked every month to check their behavior by the telenurse.“Patient Satisfaction” on tele-education and prepared materials developed by the investigators. It has 6-item with a 6-point Likert Scale, and higher indicates more satisfaction.A “Monthly outcome checklist” was developed by the investigators (Multimedia Appendix 4). The telenurses interview patients monthly asking about education material use, goal attainment, and complication management. The engagement rate and follow-up rate also will be counted every month by the telenurses.

All of the above except Diabetes management self-efficacy scale (number 3), was reviewed by the investigator team with the telenursing, diabetes, and chronic care nursing specialists for validity.

Data on all complications of diabetes will be asked of the patients by the investigators and check the accuracy of the information from the records.

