#### Research Questions

Whether implementing a health education program will improve diabetic patient outcomes or not and will be operational and acceptable by the patients and health care professionals in Bangladesh.

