#### Process of Providing Education

Figure 3 shows the 6-month program process. Because of the pilot study, we set a program for 6 months.

Right after the nurses obtain consent from participants, the nurses conduct the initial assessment using an “Initial assessment sheet” and provide educational materials (“Education booklet” and “Daily monitoring notebook”). If needed, a weight machine, BP machine, medication box, salt measurement spoon, foot care set (monofilament, mirror, nail cutter, nail file, and socks), and eye check chart will be provided. If needed, a blood glucose meter is rented to the patients.

Group education (1 group of less than 20 patients) will be provided at the PHC by the nurses on the scheduled date (1 group education is set for 2 hours).

One week after the group session, telephone calls from the nurses (telenursing education) will be provided weekly on the first month, then biweekly from the second month to the six month. The nurses will contact patients periodically over the telephone, smartphone, or tablet and follow-up on their regular dietary behavior, physical activities, and medicine compliance. They will check clinical examination and laboratory test reports, self-monitoring data, and behavior changes.

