**Figure 3 figure3:**
[figure not shown]
The 6-month program process.

In the third month, patients are requested to visit the PHC for regular follow-up by physician and laboratory test. In the sixth month group evaluation for 1 hour and endline data will be collected by the nurses at the PHC.

Patients will start implementing diabetes management right after group education. Each patient will develop monthly goal settings (behavior change plan) related to their diabetes management, daily practice them, and record the results every day in the self-monitoring notebook. The nurses call each patient on the scheduled day, ask about his or her behavior changes and monitor data, then make “step-up goals” for the next month. In addition, based on his or her knowledge and practice level, the nurses provide education using the education booklet. Patients and nurses repeat these activities for 6 months.

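### The telenurses who coach the patients also collect the self-reported outcomes, which puts those outcomes, but not HbA1c, at high risk of courtesy and social-desirability bias

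*Protocol article*

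**What the plan says.** All references are to the protocol article.

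- **Who the telenurses are.** Method of Data Collection Procedures: "The principal investigator (PI) and co-investigators (telenurses) received training in telenursing such as communication and behavior modification techniques".
- **What they deliver.** The same section, on the telenurses: "They will educate patients using an investigator-developed “Education Booklet” at the PHCs". Process of Providing Education: "telephone calls from the nurses (telenursing education) will be provided weekly on the first month", then biweekly up to month six. On these calls the nurses also agree the next month's goals with the patient.
- **What they measure.** Method of Data Collection Procedures, on the lifestyle questionnaire: "This is asked every month to check their behavior by the telenurse". On the outcome checklist: "The telenurses interview patients monthly asking about education material use, goal attainment, and complication management". On process measures: "The engagement rate and follow-up rate also will be counted every month by the telenurses".
- **Endline.** The text after Figure 3: "In the sixth month group evaluation for 1 hour and endline data will be collected by the nurses at the PHC". Quality Assurance, Control, and Data Monitoring has the research nurses collect the data and the nurses enter them, with a cross-check inside the research team.
- **Acceptability.** Research Questions asks whether the program "will be operational and acceptable by the patients and health care professionals in Bangladesh". The Hypothesis section asks whether nurses can use the system and whether providers find the program acceptable.
- **Primary outcome.** Change in HbA1c (Outcomes and Data Collection Schedule).
- **Limitations.** Selection bias, the lack of a control group and generalizability are named. Interviewer and social-desirability bias are not.

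**The concern.** A patient asked about diet, exercise or goals by the nurse who set those goals has a reason to answer favourably. That reason is weak at the first meeting and stronger after six months of coaching. In a pre/post comparison, such a change in how people answer looks the same as a change in what they do.

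The self-reported scales carry two of the three specific objectives: self-management and self-efficacy, and feasibility. They also carry the acceptability question. The Discussion foresees sharing significant results with policymakers and scaling the program up nationally if it proves effective. A favourable reporting shift could therefore be taken as support for the program. On the provider side, if the nurses using the system are investigators, the team that built the program is also judging whether providers accept it.

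**Working it through.** **1. Is it the same group of people?** The Exclusion Criteria introduce the research nurses and say that they will from then on be called simply the nurses. Process of Providing Education uses that term for those who make the calls, and the text after Figure 3 uses it for those who collect the endline data. Method of Data Collection Procedures assigns the lifestyle questionnaire and the monthly interview to the telenurses, whom it calls co-investigators. At group level, the people who deliver the program and the people who measure its outcomes are the same. Whether each patient is assessed by his or her own coach is not stated.

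**2. How much contact comes before endline?** Weekly calls in month 1, about 4. Biweekly calls over months 2 to 6, about 2 × 5 = 10. Total about 4 + 10 = 14, plus the group session.

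**3. Which outcomes are exposed?**

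| Outcome | Collected by | Exposed? |
|---|---|---|
| Lifestyle questionnaire | Telenurse, stated | Yes |
| Goal attainment, use of materials | Telenurse interview, stated | Yes |
| Self-efficacy scale | Not named; inferred from the general statements on nurses | Probably |
| Satisfaction scale | Not named; same inference | Probably, at endline only |
| Complications | Patient report checked against records | Less |
| HbA1c, primary | Laboratory value | No |

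**4. Does anything offset the shift?** There is no control group. The cross-check is internal to the team and can find recording errors, but not answers given to please. The Limitations section promises appropriate statistics to reduce bias, but no analysis can separate an unmeasured reporting shift from a real change.

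**5. Illustration of consequence.** The documents give no size for the bias, so the shift b below is an assumption. The calculation is the exact two-sided paired t test with noncentrality δ = dz × √n.

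- Check on the plan's own figure: dz = 0.39 and n = 54 give δ = 0.39 × √54 = 2.8659, critical t = 2.00575 and power 0.80335. This matches Textbox 1.
- With no true change and a pure reporting shift of b SDs of the paired differences, δ = b × √n. The chance of p<0.05 is:

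| b (assumed) | δ, n = 54 | Chance, n = 54 | δ, n = 70 | Chance, n = 70 |
|---|---|---|---|---|
| 0.1 | 0.73 | 11% | 0.84 | 13% |
| 0.2 | 1.47 | 30% | 1.67 | 38% |
| 0.3 | 2.20 | 58% | 2.51 | 70% |

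The nominal rate is 5%. The table applies to scales with a before and an after value, so it does not apply to satisfaction.

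**6. What can still be changed?** Enrolment ran from October 26, 2024 to February 2025. Adding six months puts the first endline visits around late April 2025 and the last around August 2025. The article is dated May 9, 2025, so some endline visits may already be done.

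**The case against.** The strongest reply has four parts.

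- **Mode of administration.** The article does not say who administers the satisfaction and self-efficacy scales. Collection by nurses could mean handing out and gathering self-completed forms, and the schedule is in Multimedia Appendix 5, which is not shown. This stands: for these two scales the exposure is probable, not stated. It does not help the lifestyle questionnaire or the goal interview, where the telenurse is named.
- **Who the nurses are.** Training of the Study Nurses has the nurses meeting with the investigators, and the quality section separates research nurses from investigators. Whether every telenurse is an investigator is therefore unclear, and health care professionals may include PHC physicians. This stands too. Qualitative data are also planned, so the lack of a named provider scale in a condensed article is not itself an error.
- **The causal caveat.** The Limitations section already says that no causal inference can be made. This covers why a change occurred. It does not cover whether the recorded change occurred at all, which is the issue when reporting itself shifts.
- **Harm from the remedy.** Moving the lifestyle and self-efficacy scales to self-completion at month 6, after a baseline that may have been nurse-asked, would add a mode effect of unknown direction to the paired comparison. This stands and shapes the fix.

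A reader might go further and infer that the outcomes are shown to be biased, that nearly all secondary outcomes are affected, or that satisfaction will show a spurious gain from baseline. The documents do not support this. They show a risk, not a measured bias. The full outcome list is in the appendix that is not shown, and the text also lists counts, the proportion reaching the recommended HbA1c level, and cost-effectiveness. Satisfaction with tele-education can have no value before the intervention.

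**Conclusion.** The point holds as a high risk of bias in the self-reported outcomes. It is firm for lifestyle behaviour and goal attainment, and probable for self-efficacy and satisfaction. The expected direction is favourable to the program. The size cannot be derived from the documents, and the 11% to 58% range at 54 pairs (13% to 70% at 70) rests entirely on assumed shifts of 0.1 to 0.3 SD of the paired differences.

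The HbA1c primary outcome and the sample size are untouched. The conclusion assumes only that coaching and measurement are done by one group of nurses, which the text supports. It does not assume that each coach assesses his or her own patients. Provider acceptability cannot be called an independent finding if it rests on the telenurses' own views.

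**What to change.** For month-6 visits still to come:

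1. **Satisfaction.** Patients complete the scale themselves on an ID-coded form, returned in a closed envelope before the group evaluation starts. For patients who cannot read, a telenurse who did not coach them asks the items.
2. **Lifestyle and self-efficacy.** Keep whatever mode was used at baseline, but have a telenurse who did not coach that patient administer the scales.
3. **Monthly lifestyle scores.** Treat those asked by the coach as coaching data, not as evidence of effect.
4. **Provider acceptability.** Obtain views from PHC staff who are not investigators, or state that the finding reflects the investigators' own view.
5. **Reporting.** Add interviewer and social-desirability bias to the Limitations section, and report which endline visits took place before the change.

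The cost is form handling, a change in session order and some swapping of telenurses at endline, with no extra staff and no change in sample size. The downsides are some missing items on self-completed forms and mixed procedures if part of the endline is already collected. If all endline visits are complete, items 3 and 5 and a limited provider claim under item 4 can still be done in the report.

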### Research Collaboration Framework

We will use the telenursing model with the collaboration of the Hiroshima University telenursing center and the Nursing Research Center of Grameen Caledonian College of Nursing (GCCN) (Figure 1).

**Figure 1 figure1:**
[figure not shown]
Research collaboration framework.

### Intervention

#### Operational Definition of Self-Management and Structure of the Self-Management Program

The focus of this program is the acquisition of self-management skills, operationally defined in Figure 2. First, the patients analyze their laboratory data and lifestyles including diet, and understand their condition so that they can work with their physiological data by acquiring knowledge of both the disease and self-care. By making self-supported decisions, the patients can manage their diet, exercise, and medication. They also acquire disease-specific management skills. Setting goals and then monitoring them ensures the continuation of the desired behavior and gives the patients control over their lifestyle [19].

**Figure 2 figure2:**
[figure not shown]
Structure of the self-management program.

#### Process of Providing Education

Figure 3 shows the 6-month program process. Because of the pilot study, we set a program for 6 months.

Right after the nurses obtain consent from participants, the nurses conduct the initial assessment using an “Initial assessment sheet” and provide educational materials (“Education booklet” and “Daily monitoring notebook”). If needed, a weight machine, BP machine, medication box, salt measurement spoon, foot care set (monofilament, mirror, nail cutter, nail file, and socks), and eye check chart will be provided. If needed, a blood glucose meter is rented to the patients.

Group education (1 group of less than 20 patients) will be provided at the PHC by the nurses on the scheduled date (1 group education is set for 2 hours).

One week after the group session, telephone calls from the nurses (telenursing education) will be provided weekly on the first month, then biweekly from the second month to the six month. The nurses will contact patients periodically over the telephone, smartphone, or tablet and follow-up on their regular dietary behavior, physical activities, and medicine compliance. They will check clinical examination and laboratory test reports, self-monitoring data, and behavior changes.

**Figure 3 figure3:**
[figure not shown]
The 6-month program process.

In the third month, patients are requested to visit the PHC for regular follow-up by physician and laboratory test. In the sixth month group evaluation for 1 hour and endline data will be collected by the nurses at the PHC.

Patients will start implementing diabetes management right after group education. Each patient will develop monthly goal settings (behavior change plan) related to their diabetes management, daily practice them, and record the results every day in the self-monitoring notebook. The nurses call each patient on the scheduled day, ask about his or her behavior changes and monitor data, then make “step-up goals” for the next month. In addition, based on his or her knowledge and practice level, the nurses provide education using the education booklet. Patients and nurses repeat these activities for 6 months.

### Outcomes and Data Collection Schedule

Since this is a pilot study, we set various indicators (Multimedia Appendix 5). The primary outcome is set as a change in HbA_1c_. As the secondary outcomes, we set various evaluation indicators. The data collection schedule is also set in Multimedia Appendix 5.

Sociodemographic data, clinical history, and lifestyle are taken at the initial assessment (Initial assessment sheet). Satisfaction is measured by the Likert scale (Satisfaction scale). Achievement of monthly goals is measured by percentage. Behavior change is measured by the researcher-developed scale (Lifestyle behavior questionnaire). Self-efficacy is measured by the Diabetes Management Self-Efficacy Scale.

Qualitative data will be interviewed, described, or recorded when it occurs. Engagement and follow-up rate, education material used, complication management, and “patients who have achieved HbA_1c_ in recommended level” will be counted. Cost-effectiveness will be calculated.

### Statistical Analysis

Descriptive statistics will be expressed as frequencies and percentages for categorical variables and mean with SD or median with quantile, distribution, and range for the continuous variables. To compare the categorical variables between pre- and postdata, the chi-square test will be performed. To compare feasibility and efficacy (pre and post), continuous variables will be compared by paired *t* test or one-way ANOVA for the normally distributed and or McNemar test or Wilcoxon signed-rank sum test for the not normally distributed variables after checking the data normality. Qualitative data will be described and categorized if necessary. Statistical significance will be set as <0.05. Data will be analyzed using IBM SPSS Statistics for Windows, Version 25.0 (IBM Corp).

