## Methods

### Design and Period

A pilot study with a quasi-experimental pre- and postintervention design will be implemented. As we will try to explore the participants’ characteristics, we want to conduct a pilot study to see the feasibility of this project among these participants. We plan to conduct quasi-experimental pre- and postintervention design, as we found in this setting randomization; case-control is rather difficult. Therefore, we will enroll the participants and collect baseline data and then we will educate them, and after 6 months we will evaluate them and compare the baseline (pretest) and the endline (posttest) data of individual participants. We set 6 months, as a previous study showed that a patient’s behavioral modification requires at least 6 months of intervention [18]. The study duration will be 1 year after getting approval from the Ethical Committee.

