### Sample Size

We calculated the sample size using G*Power software (version 3.1.9.7; Heinrich-Heine-University). As this is a pilot study, we set an effect size of 0.39 considering the differences between 2 dependent matched pair means of HbA_1c_ from a previous study [19], with a level of significance of 5%, and 80% power, the total sample size is calculated at 54. As patients have many options to discontinue the study (consent, withdraw, migration, change the health care facilities based on the disease severity, complications, hospitalization, etc), we consider a 30% dropout (16 participants) for this study. Therefore, the total sample size is estimated to be 70 (Textbox 1).

Output of software after generating sample size calculation.Effect size dz = 0.39α err prob = 0.05Input: Tail(s) = 2Power (1-β err prob) = 0.80Output: Noncentrality parameter δ = 2.8659030Critical *t*= 2.0057460Df = 53Total sample size = 54Actual power = 0.8033525

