### Limitations

This study has certain limitations. As we use a purposive sampling technique for selecting the study sites and participants, it causes selection bias. This is a pre- and poststudy design, not using any control group, and thus no causal inferences could be made. We will use appropriate statistics to understand associations in outcome measures to minimize biases [22]. We use 2 rural PHCs from one district; therefore, our findings cannot be generalized for the population of the whole country. Some of the enrolled patients may not understand and follow the study procedures, so we can arrange group education via video conference to minimize this.

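### Pre/post categorical outcomes are assigned the ordinary chi-square test although the same patients are measured twice, and McNemar is listed only for non-normal continuous variables

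*Protocol article*

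**What the plan says.** The design is a single group measured twice. Under Design and Period, the investigators will "compare the baseline (pretest) and the endline (posttest) data of individual participants", and Limitations confirms it: "This is a pre- and poststudy design, not using any control group". The Sample Size section builds on the pairing: "we set an effect size of 0.39 considering the differences between 2 dependent matched pair means".

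Statistical Analysis then sets two rules. For categorical variables: "To compare the categorical variables between pre- and postdata, the chi-square test will be performed". The next sentence takes continuous variables as its subject: "To compare feasibility and efficacy (pre and post), continuous variables will be compared by paired" *t* test or one-way ANOVA when normally distributed, and otherwise by "McNemar test or Wilcoxon signed-rank sum test for the not normally distributed variables after checking the data normality". No paired test is assigned to any categorical variable.

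Among the indicators under Outcomes and Data Collection Schedule is one clearly binary item, "patients who have achieved HbA_1c_ in recommended level", which the section says will be counted.

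**The concern.** The rule for categorical variables does not match the design. An ordinary chi-square test can be run on paired binary data in two ways, and neither answers the question of change:

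- On the two margins (at target before, at target after), it treats 54 patients measured twice as 108 independent patients. With positive within-patient correlation the standard error is too large, so the test is conservative and usually loses power.
- On the pre-by-post cross-tabulation, it asks whether baseline status predicts endline status. It can be highly significant when nothing has changed.

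McNemar, the standard test for change in paired binary data, appears only where it cannot be used: it has no meaning for a continuous variable, and a normality check has no bearing on it. This is a stated rule that is wrong, not a detail left to a fuller document. An analyst following the text would have no valid paired test for a categorical outcome.

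**Working it through.** **The plan's own figure.** For a paired *t* test with dz = 0.39 and two-sided alpha 0.05, n = 54 gives noncentrality 0.39 × √54 = 2.866, critical *t* = 2.006 on 53 df and power 0.8034; n = 53 gives 0.7957. The stated 54 is reproduced. It rests on pairing and on the continuous outcome, so it does not depend on the categorical rule.

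**Inputs.** From the article: 54 evaluable pairs, significance level 0.05. Assumed, because the article gives neither rates nor correlation: 30% at baseline; 30% or 45% at endline; phi of 0, 0.2, 0.3 and 0.5.

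**Why the margin version is conservative.** With N pairs and the same proportion p at both times:

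- true variance of the difference = 2p(1−p)(1−phi)/N
- variance used by the chi-square test = 2p(1−p)/N

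The chi-square test therefore rejects only when a correctly scaled *z* exceeds 1.96/√(1−phi). That is 1.96, 2.19, 2.34 and 2.77 at the four phi values, with two-sided probabilities of about 5%, 2.8%, 1.9% and 0.6%.

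**Rejection rates for 54 pairs.** Cell probabilities are p11 = p1p2 + phi√[p1(1−p1)p2(1−p2)], p10 = p1 − p11, p01 = p2 − p11, and the remainder p00. Multinomial probabilities were summed over all possible tables, with no continuity correction.

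| Scenario and test | phi 0 | 0.2 | 0.3 | 0.5 |
|---|---|---|---|---|
| 30% to 30%, chi-square on margins | 5% | 3% | 2% | 0.6% |
| 30% to 30%, chi-square on pre-by-post table | 5% | 32% | 59% | 95% |
| 30% to 45%, chi-square on margins | 37% | 35% | 34% | 31% |
| 30% to 45%, asymptotic McNemar | 37% | 44% | 49% | 61% |
| 30% to 45%, exact McNemar | 28% | 35% | 39% | 52% |

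Under no change, asymptotic McNemar stays between 4.3% and 5.4% across these phi values; exact McNemar stays between 2.4% and 3.0%.

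**Illustration 1, a change that is missed.** Of 54 patients, 16 are at target before and 25 after: 13 at target both times, 3 lost, 12 gained.

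- Chi-square on margins: pooled proportion 41/108 = 0.380; (9/54)² / (0.380 × 0.620 × 2/54) = 3.18; p = 0.074.
- McNemar: (12 − 3)²/15 = 5.4; p = 0.020.
- Exact McNemar: 2 × (1 + 15 + 105 + 455)/2¹⁵ = 0.035.

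**Illustration 2, no change but a significant result.** Of 54 patients, 12 are at target both times, 4 lost, 4 gained and 34 never at target, so 16 before and 16 after. Chi-square on the cross-tabulation: 54 × (12×34 − 4×4)² / (16×38×16×38) = 22.4, p about 0.000002. McNemar p = 1.

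**The case against.** Several points on the other side stand.

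- *The main result is safe.* The primary outcome is continuous HbA1c change, for which the plan lists the paired *t* test and Wilcoxon signed-rank. A reader might infer that the primary analysis or the sample size is invalid; the text does not support that.
- *Scope is uncertain.* The article says patients at the recommended HbA1c level will be counted, not that the proportion will be tested before against after. Engagement, follow-up rate and material use have no pre-programme value to pair. The outcome table is in Multimedia Appendix 5, which is not shown, so the number of affected outcomes cannot be established.
- *Size depends on an unstated correlation.* At phi 0.2, exact McNemar has no power advantage over the margin chi-square (35% each), and at phi 0 it has less (28% against 37%). A large loss appears only with fairly strong correlation.
- *False positives need the cross-tabulation.* A reader might infer that spurious significance is the expected result. The article speaks of comparing pre with post data; on that reading, positive correlation makes the test conservative. The 95% figure applies only if an association test is read as a test of change.
- *The tests are not swapped.* A literal swap would put chi-square on continuous variables, and Wilcoxon is already correctly placed there. McNemar is misplaced.

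One defence fails. Chi-square cannot be read as shorthand for McNemar's chi-square, because McNemar is named separately in the next sentence, under a different type of variable. If McNemar was intended for categorical data, the sentences still need correcting.

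**Conclusion.** The point holds for paired categorical secondary outcomes, such as the proportion at the recommended HbA1c level if it is compared pre to post. The mismatch between test and design follows from the text alone and needs no assumption. Its numerical effect does: with 54 pairs and 30% at baseline, it ranges from nothing at phi 0 to a margin test with a 0.6% error rate and half the power of asymptotic McNemar (31% against 61%) at phi 0.5. If the cross-tabulation is tested instead, false rejection runs from 5% to 95% over the same range. The primary analysis and the 54 pairs stand. In an uncontrolled pilot that itself disclaims causal inference, this should be fixed, but it does not undermine the main result.

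**What to change.** Rewrite the two sentences in Statistical Analysis:

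- Paired binary outcomes: McNemar test (asymptotic or mid-p; exact when discordant pairs are few), reported with the paired difference in proportions and its 95% CI.
- Paired outcomes with more than two categories: a marginal homogeneity test.
- Continuous outcomes that are not normally distributed: Wilcoxon signed-rank, with McNemar removed from this rule.

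The cost is a text change. No new data, visits or patients are needed. The Results section says analysis starts only after follow-up is complete, so the change can be made and dated before any pre/post comparison is run.

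### The plan allows one-way ANOVA for the paired HbA1c comparison, which contradicts its within-patient design and matched-pair sample size

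*Protocol article*

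**What the plan says.** All places are in the protocol article.

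- **Design and Period:** there is one group without a control, and the study will "compare the baseline (pretest) and the endline (posttest) data of individual participants" after six months.
- **Outcomes and Data Collection Schedule:** "The primary outcome is set as a change in HbA_1c".
- **Sample Size:** "we set an effect size of 0.39 considering the differences between 2 dependent matched pair means of HbA_1c_ from a previous study", "with a level of significance of 5%, and 80% power", and "the total sample size is calculated at 54". The software output in Textbox 1 shows a two-tailed test with 53 degrees of freedom, which is a paired t test on 54 differences.
- **Statistical Analysis:** for pre/post comparisons of continuous variables the plan offers a paired t test "or one-way ANOVA for the normally distributed and or McNemar test or Wilcoxon signed-rank sum test for the not normally distributed variables". The branch is chosen after a normality check. HbA1c has no separate rule, and the ANOVA is not described as repeated-measures.

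**The concern.** The design, the primary outcome and the sample size all rest on the change within each patient. One-way ANOVA does not analyse that change. With two time points it is the independent two-sample t test, so its standard error includes the between-patient variation that pairing is meant to remove.

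The paired t test and the ANOVA both sit in the branch for normally distributed data, so the normality check does not decide between them. An analyst could follow the text exactly and run the primary comparison with a test that lacks the planned power. The two tests can also disagree on the same HbA1c data.

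McNemar in the non-normal branch is a separate error in the same sentence: it compares paired binary outcomes and cannot be applied to a continuous variable.

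**Working it through.** **Inputs.** From Sample Size: dz = 0.39, two-sided alpha 0.05, n = 54 pairs. The pre-post correlation r of HbA1c is not in the document, so a range of 0 to 0.8 is assumed, with equal SDs at both times and normal data.

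**Step 1: reproduce the plan's figure.** For the paired t test the noncentrality is dz·√n = 0.39 × √54 = 2.8659, with df = 53 and critical t = 2.0057. Exact noncentral-t power is 0.8034, as in Textbox 1. With 53 pairs it is 0.7957, so 54 is the correct minimum.

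**Step 2: what the ANOVA does to the same pairs.** Let σ be the SD at each time.

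- Paired standard error: σ·√(2(1−r)/n).
- ANOVA standard error: σ·√(2/n).
- The numerator, the mean change, is the same in both.

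The ANOVA statistic, on the t scale, is therefore about √(1−r) times the paired one. It is compared with t on 2n − 2 = 106 df, critical value 1.983. In effect the paired statistic must exceed 1.983/√(1−r) instead of 2.006. At r = 0.5 that bar is 1.983/0.7071 = 2.80, and power is about Φ(2.866 − 2.80) = Φ(0.06), or 0.52 to 0.53. At r = 0.7 the bar is 1.983/0.5477 = 3.62, and power is about Φ(−0.75) = 0.23.

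**Step 3: simulation.** Correlated pairs were generated with the true mean change set to dz·√(2(1−r)) SDs for power and to zero for type I error. Independent runs of at least 40,000 replicates agree to about 0.01 in power.

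| r (assumed) | Bar on paired statistic | ANOVA power, 54 pairs | ANOVA type I error |
|---|---|---|---|
| 0 | 1.98 | 0.81 | 0.05 |
| 0.3 | 2.37 | 0.69 | 0.02 |
| 0.5 | 2.80 | 0.53 | 0.006 |
| 0.7 | 3.62 | 0.24 | below 0.001 |
| 0.8 | 4.43 | 0.07 | below 0.0001 |

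The paired t test keeps power 0.80 and type I error 0.05 in every row, because dz is already scaled by the SD of the differences.

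The usual two-sample power formula should not be used here. With 54 per time point it gives 0.52, 0.34 and 0.25 at r = 0.5, 0.7 and 0.8, but it assumes the two sets of values are independent. It therefore understates the loss at the higher correlations.

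**Step 4: pairs needed for 80% power with the ANOVA.** By the normal approximation, n = ((1.96/√(1−r) + 0.8416)/0.39)². This gives about 67 at r = 0.3, 86 at 0.5, 128 at 0.7 and 179 at 0.8. From r = 0.5 upward this is more than the 70 patients enrolled.

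**The case against.** The strongest reply is that the authors may have meant a one-way repeated-measures ANOVA. With two time points its F is the square of the paired t, and nothing is lost. A related reply is that the ANOVA was meant for outcomes measured more than twice, such as the lifestyle questionnaire, of which the article says "This is asked every month to check their behavior by the telenurse". Either is possible, but the text says neither. The sentence is limited to pre and post, and one-way ANOVA is the name of a different procedure. Both readings still need a correction to the wording.

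A reader might also infer more than the text supports:

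- *That choosing the test after a normality check discards the pairing.* It does not. The paired t test and the Wilcoxon signed-rank test are both paired; only the ANOVA option loses the pairing.
- *That the choice can be steered by the result and so produce false positives.* The stated trigger is the shape of the distribution, not the p value. The one choice without a rule, paired t or ANOVA, adds a test that is conservative when r is positive.
- *That monthly or month-3 data will be analysed as independent observations.* Nothing assigns those data to the ANOVA, and the outcome schedule is in an appendix that is not shown. This is a conditional point only.
- *That the phrase used for the Wilcoxon test brings in the unpaired rank-sum test.* The test named is the signed-rank test; the extra word is loose wording.

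Finally, a condensed article may leave analysis detail to a fuller plan. That covers what is absent. It does not cover a test list that is stated and wrong.

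**Conclusion.** The point holds as a conflict within the article: Statistical Analysis permits an unpaired test for the primary HbA1c change, while Design and Period and Sample Size require a paired one. The listing of McNemar for continuous variables is also wrong.

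The size of the harm depends on a correlation the document does not give. Under equal SDs and normal data nothing is lost at r = 0, about a third of the planned power is lost at r = 0.5 (0.80 to 0.53), and most of it is lost at r = 0.7 or above. The direction is firm for any positive correlation: the ANOVA is too conservative, and the risk is a missed effect. The planned 54 evaluable pairs are correct for the paired t test and need no change on this account. This should be corrected before the data are analysed.

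**What to change.** Before analysis starts:

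1. Name one primary analysis: the paired t test on the within-patient HbA1c difference (month 6 minus baseline), reported with its 95% CI. Keep the Wilcoxon signed-rank test as a sensitivity analysis.
2. Delete one-way ANOVA from the pre/post comparisons, and McNemar from the tests for continuous variables.
3. If ANOVA was meant for outcomes with three or more time points, say so, and specify a repeated-measures ANOVA or a linear mixed model with patient as the repeated subject.

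The cost is wording only: no new data, no change to the 54 evaluable pairs, and no change of software. According to the Results section, analysis begins only after follow-up data collection is complete, so as the article stands the test can be fixed before the results are seen.
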